### 8.1.15 MAP phase monitoring

Monitoring visits during the MAP phase will be performed at BCN-Checkpoint community center (see flow chart below). A specific MAP Phase Monitoring Form (attachment E) will be used to collect data.

During first 12 weeks post-MAP (from week 18 to week 29):

- Weekly visits will be performed, including:
  - o Clinical visit and adverse events register
  - o Reporting of symptoms suggestive of acute retroviral syndrome (including its severity grade):

|                                                  |                                                 |                                       |
|--------------------------------------------------|-------------------------------------------------|---------------------------------------|
|  Fever of unknown origin |  Headache               |  Pharyngitis  |
|  Lymphadenopathy         |  Transaminase elevation |  Lymphopenia  |
|  Oral candidiasis        |  Myalgia/arthralgia     |  Night sweats |

- |                                           |                                           |                                              |
|-------------------------------------------|-------------------------------------------|----------------------------------------------|
|  Fatigue          |  Nausea, vomiting |  Hepato/splenomegaly |
|  Rash             |  Diarrhea         |  Others              |
|  Trombochytopenia |                                           |                                              |

- 5ml blood extraction for :
  - Qualitative viral load test (Xpert HIV-1 Qual de Cepheid)
- Discussion on treatment resumption: recommendation on cART resumption will be assessed based on clinical visit, willingness of patients to resume treatment and detection of viral load in the qualitative test.
- Schedule of next appointment.
- Visits at 2, 4, 8, and 12 weeks after treatment interruptions (weeks 19, 21, 25 and 29) will also include
  - Biochemistry and hematological parameters, viral load and CD4 count (performed at an external Lab)
  - Plasma and PBMC storage following scheme detailed in attachment K
  - Discussion on treatment resumption once results from Biochemistry, Hematological parameters and CD4 cell count are available (72h): recommendation on cART resumption will be assessed based on clinical visit, willingness of patients to resume treatment, detection of viral load in the qualitative test and/or drop in CD4 cell counts.

After the first 12 weeks post-MAP (from W30):

- Fortnightly visits will be performed, including:
  - Qualitative viral load test (Xpert HIV-1 Qual de Cepheid)
  - Clinical visit, adverse event register
  - Reporting of symptoms suggestive of acute retroviral syndrome (including its severity grade)
  - Discussion on treatment resumption: recommendation on cART resumption will be assessed based on clinical visit, willingness of patients to resume treatment and detection of viral load in the qualitative test.
- Monthly:
  - Biochemistry and hematological parameters, viral load and CD4 count (performed at an external Lab)
  - Plasma and PBMC storage following scheme detailed in attachment K
  - Discussion on treatment resumption once results from Biochemistry, Hematological parameters and CD4 cell count are available (72h): recommendation on cART resumption will be assessed based on clinical visit, willingness of patients to resume treatment, detection of viral load in the qualitative test and/or drop in CD4 cell counts.

|                                                                                                           | Phase 2 (to be performed at BCN-Checkpoint) |    |    |    |    |    |    |    |    |    |    |    |                                                                |    |    |    |    |    |    |    |    |    |    |    |    |    |    |    |    |    |    |    |    |    |  |  |  |
|-----------------------------------------------------------------------------------------------------------|---------------------------------------------|----|----|----|----|----|----|----|----|----|----|----|----------------------------------------------------------------|----|----|----|----|----|----|----|----|----|----|----|----|----|----|----|----|----|----|----|----|----|--|--|--|
|                                                                                                           | 1 to 12 weeks of MAP                        |    |    |    |    |    |    |    |    |    |    |    | After the first 12 weeks of MAP (in case of no-rebound) |    |    |    |    |    |    |    |    |    |    |    |    |    |    |    |    |    |    |    |    |    |  |  |  |
| Weeks (MAP)                                                                                               | 1                                           | 2  | 3  | 4  | 5  | 6  | 7  | 8  | 10 | 11 | 12 | 13 | 14                                                             | 15 | 16 | 17 | 18 | 19 | 20 | 21 | 22 | 23 | 24 | 25 | 26 | 27 | 28 | 29 | 30 | 31 | 32 | 33 | 34 |    |  |  |  |
| Window (+/-)                                                                                              | 2d                                          | 2d | 2d | 2d | 2d | 2d | 2d | 2d | 2d | 2d | 2d | 2d | 2d                                                             | 2d | 2d | 2d | 2d | 2d | 2d | 2d | 2d | 2d | 2d | 2d | 2d | 2d | 2d | 2d | 2d | 2d | 2d | 2d | 2d | 2d |  |  |  |
| Qualitative pVL (HIV-1 Xpert Qual)                                                                        | x                                           | x  | x  | x  | x  | x  | x  | x  | x  | x  | x  | x  |                                                                |    |    |    |    |    |    |    |    |    |    |    |    |    |    |    |    |    |    |    |    |    |  |  |  |
| Clinical visit                                                                                            | x                                           | x  | x  | x  | x  | x  | x  | x  | x  | x  | x  | x  | x                                                              |    |    |    |    |    |    |    |    |    |    |    |    |    |    |    |    |    |    |    |    |    |  |  |  |
| Safety (AE and SAE)                                                                                       | x                                           | x  | x  | x  | x  | x  | x  | x  | x  | x  | x  | x  | x                                                              |    |    |    |    |    |    |    |    |    |    |    |    |    |    |    |    |    |    |    |    |    |  |  |  |
| Concomitant treatment                                                                                     | x                                           | x  | x  | x  | x  | x  | x  | x  | x  | x  | x  | x  | x                                                              |    |    |    |    |    |    |    |    |    |    |    |    |    |    |    |    |    |    |    |    |    |  |  |  |
| Biochemistry~                                                                                             |                                             | x  |    | x  |    |    |    |    |    |    |    | x  |                                                                |    |    |    |    |    |    |    |    |    |    |    |    |    |    |    |    |    |    |    |    |    |  |  |  |
| Haematology~                                                                                              |                                             | x  |    | x  |    |    |    |    |    |    |    | x  |                                                                |    |    |    |    |    |    |    |    |    |    |    |    |    |    |    |    |    |    |    |    |    |  |  |  |
| CD4 cell count~                                                                                           |                                             | x  |    | x  |    |    |    |    |    |    |    | x  |                                                                |    |    |    |    |    |    |    |    |    |    |    |    |    |    |    |    |    |    |    |    |    |  |  |  |
| Quantitative HIV-1 pVL~                                                                                   |                                             | x  |    | x  |    |    |    |    |    |    |    | x  |                                                                |    |    |    |    |    |    |    |    |    |    |    |    |    |    |    |    |    |    |    |    |    |  |  |  |
| Plasma and PBMC storage#                                                                                  |                                             | x  |    | x  |    |    |    |    |    |    |    | x  |                                                                |    |    |    |    |    |    |    |    |    |    |    |    |    |    |    |    |    |    |    |    |    |  |  |  |
| Efficacy Endpoint                                                                                         |                                             | x  |    |    |    |    |    |    |    |    |    | x  |                                                                |    |    |    |    |    |    |    |    |    |    |    |    |    |    |    |    |    |    |    |    |    |  |  |  |
| # to be shipped to HGTP for processing in the same day (for virological and immunological studies)        |                                             |    |    |    |    |    |    |    |    |    |    |    |                                                                |    |    |    |    |    |    |    |    |    |    |    |    |    |    |    |    |    |    |    |    |    |  |  |  |
| ~ to be shipped to General Lab : results available at Checkpoint (Report by phone to the patients at 72h) |                                             |    |    |    |    |    |    |    |    |    |    |    |                                                                |    |    |    |    |    |    |    |    |    |    |    |    |    |    |    |    |    |    |    |    |    |  |  |  |

If qualitative pVL test is found positive (indicative of pVL >200 copies/ml), following procedures will be performed:

- Blood extraction including:
  - o Viral load, hematological parameters and CD4 count
  - o Plasma and PBMC storage following scheme detailed in attachment K
  - o pVL-pos+3d visit scheduling

pVL-pos+3d visit will be performed at BCN-Checkpoint and will include:

- Clinical visit, adverse event collection
- Reporting of symptoms suggestive of acute retroviral syndrome (including its severity grade)
- Blood extraction including:
  - o Viral load and CD4 count
  - o Genotype resistance test
  - o Plasma and PBMC storage following scheme detailed in attachment K
- cART resumption visit scheduling (pVL-pos + 7 days) at BCN-Checkpoint

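### Section 8.1.15 contradicts itself on the week-8 visit of the antiretroviral pause: the text requires a blood panel that the schedule table leaves blank

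*Protocol*

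**What the plan says.** Section 8.1.15 describes weekly visits for the opening part of the pause: "During first 12 weeks post-MAP (from week 18 to week 29"). It then adds a larger panel at selected visits: "Visits at 2, 4, 8, and 12 weeks after treatment interruptions (weeks 19, 21, 25 and 29) will also include" the following. The list opens with "Biochemistry and hematological parameters, viral load and CD4 count (performed at an external Lab") and continues with plasma and PBMC storage. A discussion of treatment resumption follows once those results are back, and a fall in CD4 count is one of its inputs.

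The same section refers the reader to a chart for the visits at the community centre. That chart has a band headed "1 to 12 weeks of MAP". Its rows "Biochemistry", haematology, "CD4 cell count", "Quantitative HIV-1 pVL" and plasma/PBMC storage each carry a mark in the second, fourth and twelfth columns and nowhere else. The row "Efficacy Endpoint" is marked in the second and twelfth columns.

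Secondary endpoint 3.4 (section 5.3.2) and section 10.1 both set the viral-control endpoint at 12 weeks after cessation; section 10.1 also gives it as study week 29.

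**The concern.** Two statements of one schedule, in one section, disagree on whether a panel is drawn at week 8. The participants are off antiretroviral therapy at that point. A CD4 decline is among the criteria for restarting treatment in secondary endpoint 3.5 and section 8.1.16, and the weekly qualitative test does not measure CD4.

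The panel also supplies the routine safety bloods and the stored plasma and cells for the virological and immunological studies. A stored sample that was not taken at week 8 cannot be recovered later. If some visits follow the text and others the table, the week-8 data will be incomplete for a reason unrelated to the participants. No sample size, error rate or power figure depends on this point.

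**Working it through.** This is a calendar check and a count of table cells.

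**1. The text's own calendar.** Interruption is at study week 17 (section 8.1.14).
- 17 + 2 = 19, 17 + 4 = 21, 17 + 8 = 25, 17 + 12 = 29. These are the study weeks that the text gives.
- Weeks 18 to 29 inclusive: 29 − 18 + 1 = 12 weekly visits.

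The text is internally consistent, and it states week 8 in both notations.

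**2. The table, by column position.**

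| Row | Marked columns | Column 8 |
|---|---|---|
| Qualitative viral load | 1 to 12 | marked |
| Clinical visit, safety, concomitant treatment | 1 to 13 | marked |
| Biochemistry | 2, 4, 12 | blank |
| Haematology | 2, 4, 12 | blank |
| CD4 count | 2, 4, 12 | blank |
| Quantitative viral load | 2, 4, 12 | blank |
| Plasma/PBMC storage | 2, 4, 12 | blank |
| Efficacy endpoint | 2, 12 | blank |

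**3. Could a label error explain the gap?** The printed week labels run 1 to 8 and then 10 to 34.
- Number of labels: 8 + (34 − 10 + 1) = 33. The window row has 34 entries, so one label, the 9, is missing and the later labels sit one column to the left.
- Columns 1 to 8 come before the slip and are labelled correctly. The blank column 8 is therefore week 8, and restoring the 9 does not fill it.
- With the 9 restored, the twelfth column reads week 12, which is study week 17 + 12 = 29. This agrees with the text and with section 10.1.

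**4. Size of the discrepancy in the first 12 weeks** (ignoring the ±2-day windows).
- Text: panels at 2, 4, 8 and 12; intervals 2, 2, 4 and 4 weeks; longest 4.
- Table: panels at 2, 4 and 12; intervals 2, 2 and 8 weeks; longest 12 − 4 = 8.
- Scheduled panels: 4 against 3. The missing one is at study week 25.

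**5. What still covers weeks 4 to 12 if the table is followed.** Qualitative testing and clinical review are weekly in both text and table. Section 8.1.15 treats a positive qualitative test as indicating more than 200 copies/ml. A positive result triggers quantitative viral load, haematology, CD4 and storage, with viral load, CD4 and storage again three days later. That signal level is 2,000 / 200 = 10 times below the 2,000 copies/ml used in the endpoint. The unprotected gap is therefore confined to participants whose qualitative tests stay negative, and it concerns CD4, safety bloods and stored samples more than detection of rebound.

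**6. Efficacy marks.** The twelfth-column mark fits the 12-week endpoint. The second-column mark has no counterpart in secondary endpoint 3.4 or section 10.1, neither of which defines a week-2 efficacy reading.

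**The case against.** The strongest objection is that the table may be damaged. A label has been lost, and no row has a mark beyond the thirteenth column, although the columns run to week 34 and the text requires fortnightly qualitative tests and monthly bloods after week 12. If marks were lost there, they may also have been lost at week 8, and agreement among five rows is then weaker evidence than it looks. This stands as a reason to check the source page first. It does not dispose of the point: column 8 kept its marks in four other rows, and the five blank rows kept theirs at 2, 4 and 12.

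It can also be said that the text is explicit, and that section 8.1 refers sites to Attachment J for the detailed schedule. Attachment J is not available here and may settle what sites do. It would not remove the disagreement within section 8.1.15.

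The harm is also bounded by the weekly qualitative test and the reflex draws that follow a positive result. That is correct.

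A reader might infer more from the printed labels: that the endpoint is read a week late because the last efficacy mark stands under 13, that the week-9 qualitative test is omitted, that weekly testing has a two-week hole, or that the interval without bloods is 9 weeks. The documents do not support these readings. The band has twelve columns and twelve qualitative marks, matching twelve weekly visits. There is one label fewer than there are window entries, and both the text and section 10.1 fix week 29.

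**Conclusion.** The contradiction on the week-8 panel holds, subject to the source page showing the same blanks. One of four panels required by the text is absent from the table in all five rows. The longest scheduled interval without CD4, safety bloods or stored samples is 8 weeks by the table and 4 by the text. In practice this affects participants whose qualitative tests remain negative. Detection of rebound for the Part B endpoint is largely protected by weekly qualitative testing.

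The missing week-9 label and the week-2 efficacy mark are secondary and need tidying; neither shows a different endpoint time. The point should be corrected because it bears on monitoring of participants off therapy and costs little. Confidence is moderate, given the condition of the table as read and the attachments not seen. Which week-8 schedule is right is for the sponsor and investigators to settle.

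**What to change.** 1. Compare the table in section 8.1.15 with the source page, in particular the week-8 cells, the column labels and the nearly empty area after week 12.
2. If the week-8 cells are blank there, reconcile text and table so that both say the same about the week-8 panel (biochemistry, haematology, CD4, quantitative viral load, storage). Confirm that Attachments E, J and K agree.
3. If the week-9 label is missing there, restore it so that the twelve columns read 1 to 12.
4. Align the efficacy row with the 12-week endpoint in secondary endpoint 3.4 and section 10.1, and either explain or remove the week-2 mark.

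The cost is a check of one page and a correction to one table, or to the text if that is what changes, plus a check of the attachments. The analysis does not change.

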#### **8.1.14 MAP – Monitored antiretroviral pause and MVA2+8w – Eight weeks post MVA2 vaccination (17 weeks)**

Following procedures will be performed at both clinical sites (HGTIP and HC):

- Blood extraction including:
  - Viral load, biochemistry and hematological parameters.
  - Plasma and PBMC storage following scheme detailed in attachment K
- cART adherence assessment (SERAD questionnaire)
- Clinical visit, adverse event register
- Review acceptability for cART interruption after interim analyses (which will be performed at week 13 and be provided by investigational team in advance and recorded in 'Indication for MAP phase' form, attachment X)
- Review acceptability for cART interruption regarding plasma viral load suppression (pVL below the limit of detection in 2 consecutive determinations, spaced at least 1 week, and recorded in 'Indication for MAP phase' form, attachment X)
- Phase 2 study explanation including: cART interruption, site, weekly clinical visit, qualitative plasma viral load monitoring, criteria for cART resumption.
- CRF data collection

Once analytical results are available, cART interruption will be confirmed telephonically by study physician and first visit in BCN-Checkpoint will be scheduled.

In cases where pVL is not undetectable for 2 consecutive determinations, MAP will be postponed and extra visits will be scheduled (every week if pVL is 20-500 copies/mL, every two weeks if pVL is >500 copies/mL) including the following procedures until acceptability criteria for cART interruption are met.

- Blood extraction including:
  - Viral load, biochemistry and hematological parameters.
  - Plasma and PBMC storage.
- cART adherence assessment (SERAD questionnaire)
- Clinical visit, adverse event register

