#### 8.1.16 cART resumption visit (7-10 days after first Qual pVL positive)

pVL-pos+7d visit will be performed at BCN-Checkpoint.

Following procedures will be performed:

- Reporting of symptoms suggestive of acute retroviral syndrome (including its severity grade)
- Discussion on treatment resumption based on following considerations (attachment M):
  - o If viral load is >2,000 copies/mL in visits pVL-pos and pVL-pos+3d, and/or clinical symptoms, laboratory abnormalities or significant drops in CD4 T cell counts (>50% &/or <500) have been detected, patients will be recommended to re-start cART immediately.
  - o If viral load is <2,000 copies/mL in visits pVL-pos and >2,000 copies/mL in visit pVL-pos+3d, and/or clinical symptoms, laboratory abnormalities or

significant drops in CD4 T cell counts (>50% &/or <500) have been detected, patients will be recommended to re-start cART immediately.

- If viral load is > or <2,000 copies/mL in visits pVL-pos and <2,000 copies/mL in visit pVL-pos+3d, and NO clinical symptoms, laboratory abnormalities or significant drops in CD4 T cell counts have been detected cART will not be resumed.
- cART prescription\* at the Pharmacy Unit
- Follow-up explanation and cART+4w visit scheduling (or a follow-up MAP visit at BCN-Checkpoint if cART is not resumed)
- CRF data collection

\*cART regimen will at the discretion of the study physician, according to clinical criteria (no changes on patient's previous cART regimen are envisioned as no emergence of drug resistances is expected)

Overall, time since 1st positive HIV-1 Qualitative detection to cART resumption is aimed to be <10 days to avoid fast viral reservoir replenishment.

[figure not shown]

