## 8.2 CART+4W, CART+12W – CART FOLLOW-UP VISITS (4 AND 12 WEEKS AFTER CART RESUMPTION)

As when naïve HIV positive individuals start 1st line treatment, all individuals will be followed to monitor clinical, virological and immune outcomes after cART resumption.

Following procedures will be performed:

- Blood extraction including:
  - Viral load, biochemistry and hematological parameters and CD4 count
  - Plasma and PBMC storage following scheme detailed in attachment K

- Clinical visit, adverse event register
- cART adherence assessment (SERAD questionnaire)
- Next visit scheduling
- CRF data collection

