#### 8.4.2 Laboratory tests

Patients will fast for at least 8 hours prior to assessment, in the points specified in the schedule of procedures of the study (attachment J), except for RMD1 assessment that will be performed in the evening previous RMD1 administration. The following parameters will be quantified, as needed:

- **Hematology:**
  - Hematocrit
  - Red blood cell count
  - Hemoglobin
  - Leucocytes
  - Lymphocyte
  - Platelet count
- **Blood biochemistry:**
  - Urea
  - Creatinine
  - Ionogramme: sodium, potassium
  - Total Bilirubin
  - Total protein
  - Albumin
  - Liver enzymes: aspartate aminotransferase (AST), alanine aminotransferase (ALT), gamma-GT, alkaline phosphatase
  - Estimated glomerular filtration rate (CKD-EPI)
  - Creatinin Kinase (CK)

**Extra ions:** Magnesium, phosphate and calcium

- **Pregnancy test in women (test strip)**
- **Immunology:**
  - CD4 lymphocytes count
  - CD4 lymphocytes percentage
  - CD8 lymphocytes count
  - CD8 lymphocytes percentage

**Note:** Before the beginning of the study, all labs will facilitate to the sponsor and to the investigator a list of the reference normal values of the parameters assessed.

- **Specific Lab Procedures**  
To be assessed along the study, as detailed in the endpoint section 5.3:
  - Romidepsin concentrations in plasma will be determined by liquid chromatography–mass spectrometry (LC-MS) / mass spectrometry (MS)
  - HIV-1 DNA in CD4 T cells by ddPCR
  - Cell-associated RNA (CA-RNA)

- Viability, necrosis and apoptosis levels by flow cytometry
- Activation, exhaustion and proliferation capacity by flow cytometry
- IFNg production assessed by ELISPOT
- In-vitro viral inhibition capacity
- Ultrasensitive plasma viral load (SCA)
- Histone H3 acetylation in lymphocytes

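### The rebound work-up lists no biochemistry, although staying off cART requires that no laboratory abnormalities have been found

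*Protocol*

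**What the plan says.** After a positive qualitative test, Protocol section 8.1.15 lists the blood work as "Viral load, hematological parameters and CD4 count", plus storage. The visit three days later lists viral load, CD4, a resistance genotype and storage. Section 8.1.16, the visit at day 7 to 10 where resumption is decided, lists no blood draw.

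Section 8.1.16 recommends restart if viral load exceeds 2,000 copies/ml at day 3, or if there are symptoms, laboratory abnormalities or a significant CD4 fall. The one branch that leaves a viraemic participant off treatment requires less than 2,000 copies/ml at day 3 "and NO clinical symptoms, laboratory abnormalities or significant drops in CD4 T cell counts have been detected cART will not be resumed".

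The checklist of acute retroviral signs in 8.1.15 includes "Transaminase elevation". Section 8.4.2 places "Liver enzymes: aspartate aminotransferase (AST), alanine aminotransferase (ALT), gamma-GT, alkaline phosphatase" under blood biochemistry, not haematology.

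Routine biochemistry during the pause is tied to a few visits: "Visits at 2, 4, 8, and 12 weeks after treatment interruptions (weeks 19, 21, 25 and 29) will also include" it, and after week 12 it is monthly. At those visits 8.1.15 provides for a resumption discussion once the biochemistry, haematology and CD4 results are back, with a stated 72-hour turnaround.

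Elsewhere the protocol names biochemistry when it wants it: "Viral load, biochemistry and hematological parameters" at the week 17 visit (8.1.14), and "Viral load, biochemistry and hematological parameters and CD4 count" after cART resumption (8.2).

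**The concern.** The rule in 8.1.16 relies on laboratory abnormalities as a category separate from CD4 falls, but the work-up feeding it measures only part of that category. Lymphopenia and thrombocytopenia, the other laboratory items on the checklist, can be read from the haematology drawn on the day of the positive test. A transaminase rise cannot be read from any listed work-up draw. A finding of no abnormality may therefore mean only that liver enzymes were not measured.

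This matters in one branch. Above 2,000 copies/ml at day 3, restart is recommended on viral load alone and biochemistry changes nothing. Below it, with no symptoms, haematological abnormality or CD4 fall, the participant stays off cART. That decision then rests on a liver panel that may predate the detected rebound. At stake is a delay in recognising a sign that the protocol itself treats as grounds for restarting. Endpoints 3.4 and 3.5 are not claimed to be misclassified.

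**Working it through.** The protocol gives no figure to reproduce. The check lays the draws side by side and then counts visits.

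**What each step measures**

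| Step | Viral load | CD4 | Haematology | Biochemistry (AST/ALT) |
|---|---|---|---|---|
| Scheduled laboratory visit in the pause (8.1.15) | yes | yes | yes | yes |
| Day of positive test (8.1.15) | yes | yes | yes | not listed |
| Day 3 (8.1.15) | yes | yes | not listed | not listed |
| Decision visit, day 7 to 10 (8.1.16) | no draw listed | no draw listed | no draw listed | no draw listed |

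**Inputs for the count.** Visits are weekly in pause weeks 1 to 12. Panels fall at week 0 (the MAP visit, 8.1.14) and weeks 2, 4, 8 and 12 (8.1.15 text; the flow table is broken in the copy available, so the text weeks are used). Turnaround is 72 hours, and the decision is taken from day 7.

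**Formulas.** Let w be the week of the first positive test, L the last panel week before w, and N the next panel week after w.

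- Age of the last panel at day 7 = (w − L) + 1 weeks, ignoring any panel drawn on day 7 itself
- Wait for the next scheduled panel = N − w weeks
- Its result = day 7 × (N − w) + 3

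At w = 2, 4, 8 and 12 a panel is drawn the same day. The other eight weeks give:

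| w | L | N | Age at day 7 (weeks) | Wait for next panel (weeks) | Result available |
|---|---|---|---|---|---|
| 1 | 0 | 2 | 2 | 1 | day 10 |
| 3 | 2 | 4 | 2 | 1 | day 10 |
| 5 | 4 | 8 | 2 | 3 | day 24 |
| 6 | 4 | 8 | 3 | 2 | day 17 |
| 7 | 4 | 8 | 4 | 1 | day 10 |
| 9 | 8 | 12 | 2 | 3 | day 24 |
| 10 | 8 | 12 | 3 | 2 | day 17 |
| 11 | 8 | 12 | 4 | 1 | day 10 |

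**Results**

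- No same-day panel: 12 − 4 = 8 of 12 weeks.
- If scheduled visits continue during the work-up, weeks 1, 3, 7 and 11 get a panel about day 7, with the result about day 10, the end of the decision window.
- Weeks 5, 6, 9 and 10 (4 of 12) get no panel by the decision. The last one is then 2 to 3 weeks old, and the next is drawn 2 to 3 weeks after the positive test.
- After week 12, tests are fortnightly and panels monthly, so about half of the test visits carry a panel.

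**With biochemistry added to the work-up draws.** A day 0 draw reports on day 0 + 3 = day 3, and a day 3 draw on day 3 + 3 = day 6. Both precede the decision for a first positive at any of the 12 weeks, if the 72-hour turnaround applies to these draws too.

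**The case against.** The strongest reply is that the running text may not be the full specification. Section 8.1 refers the detailed schedule to attachment J, and 8.1.16 refers the decision to attachment M. Neither is shown, and the draw lists are introduced as inclusive. An attachment could already order the panel, and section 9.2 lets an investigator use other appropriate tests. This stands as a limit on certainty. The text would still need aligning, because it names biochemistry at other visits and omits it here.

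It can also be said that 8.1.16 does not define laboratory abnormalities as transaminases, that the checklist is used weekly without a panel each time, that the shorter symptom list in 8.4.1 omits transaminases, and that endpoint 3.5 does not name liver enzymes. The rule can indeed run on haematology alone. But 8.1.15 makes biochemistry an input to resumption discussions at scheduled visits, and it is hard to see why it should drop out once rebound is suspected.

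Third, the decision is revisited: follow-up visits continue, and the next panel in weeks 1 to 12 comes 1 to 3 weeks after the positive test. Most cases would be a delay; only a rise that resolves before that panel would be missed outright. This is fair.

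Fourth, nothing in the text cancels scheduled visits during the work-up, so 4 of 12 is better supported than 8 of 12. With the 2-day visit window, a panel due on day 7 could be drawn on day 5 and reported on day 8. It could equally be drawn on day 9 and reported on day 12, after the window closes. The count of 8 remains correct for same-day coverage and is an upper bound for the decision.

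Finally, few participants will be in the affected branch with an isolated transaminase rise. That is probably right, and the document gives no means of quantifying it.

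**Conclusion.** The concern holds. As written, the rebound work-up cannot reliably verify one of the conditions for leaving a viraemic participant off cART. In the first 12 weeks of the pause, between 4 and 8 of 12 possible first-positive visits lack timely biochemistry: 4 if scheduled visits continue during the work-up, 8 if they do not. At a day-7 decision without a new panel, the last one is 2 to 4 weeks old, or 2 to 3 weeks in the four weeks that are uncovered either way.

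These are counts of visits, not probabilities of rebound or harm. They rest on the panel weeks in the text of 8.1.15, on the 72-hour turnaround, and on the unseen attachments not adding the panel. The effect is a delay in participant safety monitoring. No sample size, error rate or endpoint definition is affected. Because the condition concerns safety and the remedy is cheap, it should be corrected.

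**What to change.** In section 8.1.15, add biochemistry to the blood-draw list for the day of the positive qualitative test, and preferably to the day 3 list as well. AST and ALT are the results the argument depends on; creatinine comes with the same panel. Bring attachments J, K and M into line if they differ. The restart criteria in 8.1.16 need no change.

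The cost is one routine panel per rebound draw, on venepunctures already planned, and one added word in each list. No new visit is needed.
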